## 7.3 Procedures for assessing safety

A symptom evaluation and targeted physical examination will be performed at each visit.

Body composition changes will be evaluated at baseline, annual visits and the final study visit as follows:

- Waist circumference will be measured between the lower border of the ribs and the iliac crest, in a horizontal plane.
- Hip circumference will be measured at the widest point over the buttocks.
- Patients will be asked about any change in fat in the face, arms, legs or abdomen. Taking into account the patient's opinion, the research nurse or doctor will grade facial lipoatrophy as none, moderate (evident on inspection), or severe (immediately obvious).

Patients will be asked about symptoms of peripheral neuropathy at baseline, annual visits and the final study visit. A brief neuropathy examination will be performed at baseline and the final study visit in all patients, and at intervening annual study visits if the patient reports neuropathy symptoms

Cardiovascular risk factors will be assessed at annual trial visits, and risk will be quantified using the Joint British Societies cardiovascular risk prediction charts (see Appendix 11).

Blood will be drawn at trial visits to assess laboratory safety parameters according to standard-of-care as indicated in the schedule of trial assessments (see section 1.3). Additional safety blood tests or investigations will be performed to investigate symptoms or monitor emergent laboratory test abnormalities as clinically indicated.

All adverse events will be reported on the case report form. Adverse events (clinical and laboratory) will be graded using the 2004 Division of AIDS toxicity grading scale (see Appendix 7). Serious adverse events will be defined according to the EU Directive 2001/20/EC Article 2 based on ICH GCP, and will be reported to the MRC CTU for the duration of the main trial i.e. whilst patients are attending trial visits according to standard timelines (see section 11).

Diagnostic criteria for selected serious AIDS and non-AIDS events are defined in the protocol (see section 9.2.2 and Appendices 8 and 9), and sites will be encouraged to investigate patients in a way that allows determination of whether patients meet the specified diagnostic criteria. An independent endpoint review committee will review these endpoints to ensure that they satisfy the criteria.

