| Cervical carcinoma, invasive                    | none                                                                                                                                                                                                                                                                                                                                 | histology, not carcinoma-in-situ                                                          |
| NEUROLOGICAL                             |                                                                                                                                                                                                                                                                                                                                      |                                                                                           |
| HIV encephalopathy                              | Cognitive or motor dysfunction interfering with usual activity, progressive over weeks or months in the absence of another condition to explain the findings, should have brain scan +/- CSF to exclude other causes. should be grade 2 or worse in at least 2 domains by NARS (see below) excluding abnormal domains at trial entry | none                                                                                      |
| OTHER                                    |                                                                                                                                                                                                                                                                                                                                      |                                                                                           |
| Indeterminate intracerebral lesion(s)           | Neurological illness with evidence for an intracerebral lesion(s) by brain scan where the differential diagnosis is either cerebral toxoplasmosis, PML, cerebral lymphoma or HIV encephalopathy                                                                                                                                      | none                                                                                      |

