| Acute liver failure                                                                       | ALT or AST greater than 5 times ULN, with clinical jaundice and encephalopathy.                                                                                                                                                                                                                                                                                                                                                                                                                                                                                                                                                                                                                                                                                                                    |
| End-stage renal disease                                                                   | A or B or C: (A) Haemodialysis or peritoneal dialysis for a period of at least three months, documented in a clinical note; (B) A kidney transplant, documented in a clinical note; (C) two consecutive measurements of serum creatinine clearance rate < 15 ml/min per 1.73 m  calculated using the Cockcroft-Gault equation.                                                                                                                                                                                                                                                                                                                                                                                                                                                         |

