| Severe peripheral neuropathy                                                              | Severe pain, numbness or tingling in the feet and/or legs that interferes with normal activities and requires narcotic analgesia for control.                                                                                                                                                                                                                                                                                                                                                                                                                                                                                                                                                                                                                                                      |
| Non-AIDS malignancy (excluding Kaposi's sarcoma (KS), lymphoma, invasive cervical cancer) | Diagnosis of cancer other than lymphoma, KS or invasive cervical cancer and a written report in the medical record from the hospitalisation during which the diagnosis was established, or in a pathology report that established the diagnosis, or in an autopsy report.                                                                                                                                                                                                                                                                                                                                                                                                                                                                                                                          |

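### Appendix 8 lets a minor skin cancer, and a kidney injury that recovers, qualify as serious non-AIDS events: malignancy has no skin exclusion and is silent on in-situ disease, and renal criterion C has no persistence condition

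*Combined protocol and SAP*

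**What the plan says.** Section 9.2.2 defines the secondary outcome of serious drug or disease-related complication as a patient's first event from a list: death, serious AIDS-defining illness and eleven serious non-AIDS conditions. All count equally. Section 9.5.2 analyses it by time-to-event methods. Appendices 7 and 8 hold the diagnostic criteria.

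- **Malignancy (Appendix 8).** The criterion is "Diagnosis of cancer other than lymphoma, KS or invasive cervical cancer and a written report in the medical record" from the diagnosing hospitalisation, "or in a pathology report that established the diagnosis, or in an autopsy report". These are three alternative forms of documentation, so admission to hospital is not required.
- **Cervical carcinoma (Appendix 7).** The definitive criterion is "histology, not carcinoma-in-situ".
- **End-stage renal disease (Appendix 8).** Any one of three criteria is enough. A is "Haemodialysis or peritoneal dialysis for a period of at least three months, documented in a clinical note". B is a kidney transplant. C is "two consecutive measurements of serum creatinine clearance rate < 15 ml/min per 1.73 m"², calculated with the Cockcroft-Gault equation.
- **Testing between visits (section 7.3).** "Additional safety blood tests or investigations will be performed to investigate symptoms or monitor emergent laboratory test abnormalities as clinically indicated".
- **Adjudication (sections 7.3 and 16.4).** The Endpoint Review Committee checks whether reported events meet the written criteria.

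**The concern.** A composite of serious events is easiest to interpret when everything in it is serious and correctly named. Two entries can fail that test.

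A small skin cancer treated in clinic meets the malignancy wording. In a first-event analysis it carries the same weight as a death, and it removes that patient's later infarction or stroke from the composite. If such lesions are unrelated to the randomised strategy, they also pull the hazard ratio towards 1. That could mask harm from PI monotherapy as readily as benefit.

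The renal entry has a different problem. A patient who is briefly very ill, has two low clearances and then recovers would be reported as having end-stage renal disease. The event is serious, but the label is wrong, and the label matters when components are reported separately. Renal function is of interest here: creatinine is measured throughout the trial and is one of the few laboratory values kept for the extension phase (section 18).

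**Working it through.** **Reproducing a plan figure.** None exists. The documents give no event rate, effect size or power for this composite. The 554 patients in section 9.3 relate to the drug-resistance endpoint.

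**Text check: malignancy**

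| Case | Appendix 7 | Appendix 8 |
|---|---|---|
| Basal cell carcinoma with pathology report | Not listed | Meets the wording; no exclusion applies |
| Carcinoma-in-situ of the cervix | Excluded in words | Not addressed; turns on whether in-situ disease is a cancer |
| Carcinoma-in-situ elsewhere | Not listed | Not addressed; same question |

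Appendix 8 removes only invasive disease of the cervix, so it does not settle the second row.

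**Text check: renal**

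1. Criterion A has a duration (three months). Criterion C has a count (two consecutive values) but no interval, persistence or irreversibility condition.
2. After week 12, scheduled biochemistry is nominally every 12 weeks, with windows of ±6 weeks (section 7.1.4). Two values days apart would therefore normally come from the unscheduled tests that section 7.3 allows, which is the acute-illness setting.
3. A patient dialysed for less than three months fails A but can still qualify under C on two earlier results. A's duration requirement can thus be bypassed.
4. Cockcroft-Gault returns ml/min, not indexed to body surface area. Indexing needs height. Sections 5.1 and 7.1.5 list weight, waist and hip circumference; no visit lists height.

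**Illustration of dilution: skin and in-situ events only.** Every rate and hazard ratio below is an assumption.

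Let *f* be the share of control-arm composite events that treatment does not affect. Then observed HR = (1 − *f*) × true HR + *f*.

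| True HR | *f* = 5% | *f* = 30% |
|---|---|---|
| 0.50 | 0.53 | 0.65 |
| 0.67 | 0.69 | 0.77 |
| 1.5 | 1.48 | 1.35 |
| 2.0 | 1.95 | 1.70 |

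The same thing in rates: uniform accrual over 24 months of a 60-month trial (section 9.3) gives follow-up of 36 to 60 months, mean 48. Before losses that is 280 × 4 = 1120 patient-years per arm. Assume 1.0 other composite events per 100 patient-years in the control arm, and 0.2 to 0.5 minor events per 100 in both arms.

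- *f* = 0.2/1.2 = 17% to 0.5/1.5 = 33%.
- True HR 0.60: (0.6 + 0.2)/1.2 = 0.67 to (0.6 + 0.5)/1.5 = 0.73.
- True HR 2.0: (2.0 + 0.2)/1.2 = 1.83 to (2.0 + 0.5)/1.5 = 1.67.

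Precision on the same inputs, with standard error of log HR = √(1/events₁ + 1/events₀):

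- Undiluted HR 0.60: 11.2 control and 6.7 monotherapy events, 95% CI about 0.23 to 1.56.
- Diluted HR 0.73: 16.8 and 12.3 events, 95% CI about 0.35 to 1.53.

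Both intervals include 1.

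**The case against.** There is a good deal to be said for leaving the text alone.

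- **The criteria are borrowed deliberately.** Appendix 8 says they are based on those of an established endpoint-trial network, and malignancy and end-stage renal disease are not among the entries it names as added. Comparability is a real benefit. It does not remove the gaps, but it is a cost of closing them.
- **Very low clearance is not minor.** It is grave and may be drug-related. The composite does not require irreversibility: pancreatitis and lactic acidemia can recover, and lactic acidemia also uses two consecutive values with no interval. This stands. The renal fault is a wrong label, and a reader who infers that these events dilute the composite goes beyond the documents.
- **In-situ disease is never mentioned.** A reader might infer that any carcinoma-in-situ counts. Appendix 8 requires a diagnosis of cancer, and whether that covers in-situ disease is open. Only the ambiguity is established.
- **The committee could use judgement.** Section 16.4 does not say how it should treat doubtful wording, so it cannot be claimed that it would have to accept every such case. Equally, no power to set aside a qualifying event is described.
- **Little may turn on it.** This is one of eight secondary outcomes with no power claim. Grade III and IV events are a separate outcome, serious adverse events are reported separately, and the illustrated intervals are wide with or without dilution. This limits the weight of the point but does not answer it.

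**Conclusion.** The point holds as one about definitions. The malignancy criterion, as written, admits non-melanoma skin cancer and leaves in-situ disease undecided. Renal criterion C admits reversible acute kidney injury under an end-stage label, and its unit does not match its equation.

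The effect is confined to one secondary composite and its renal component, including the serious non-AIDS events collected in the extension phase if the same criteria are applied there. The primary endpoint and sample size are untouched.

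The size of any dilution cannot be derived. The illustrated shifts rest on assumed rates and on minor events being unrelated to treatment, and they include no renal events. A reader might take a 17% to 33% share as a finding about this trial; it follows only from the rates chosen. Nor do the documents call this composite the main clinical safety comparison.

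This is a cheap improvement, not a flaw that threatens the trial's conclusions.

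**What to change.** Amend two entries in Appendix 8:

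1. **Non-AIDS malignancy:** exclude basal cell carcinoma of the skin, non-metastatic squamous cell carcinoma of the skin, and carcinoma-in-situ at any site. Excluding all squamous skin cancer would go too far, because it would drop metastatic disease.
2. **End-stage renal disease, criterion C:** add a persistence condition comparable to criterion A, for example two values at least three months apart, and state the limit in ml/min, the unit Cockcroft-Gault gives.

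Give both changes to the Endpoint Review Committee before it reviews events. In an open-label trial, settling these cases in advance is better than deciding them one by one.

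The cost is two edited entries, slightly fewer composite events and some loss of comparability with the network's criteria. During the main trial, excluded events are still reported as adverse events. Section 18 requires no serious adverse event reporting in the extension phase, so if excluded cancers are wanted there, the annual notes review should record them separately.

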#### 9.2.2 Secondary outcome measures

- **Serious drug or disease-related complication**

Defined as the first occurrence of one of the following in any individual patient:

- **Death from any cause**
- **Serious AIDS-defining illness** (see diagnostic criteria, Appendix 7)
- **Serious non-AIDS defining illness** (see diagnostic criteria, Appendix 8)
  - Acute myocardial infarction
  - Coronary artery disease requiring invasive procedures
  - Cirrhosis
  - Acute liver failure
  - End-stage renal disease
  - Stroke
  - Clinical acute pancreatitis
  - Severe lactic acidemia
  - Severe facial lipoatrophy
  - Severe peripheral neuropathy
  - Non-AIDS malignancy

- **Adverse events**

Defined as the total number of Grade III and IV adverse events.

- **Confirmed Virological rebound**

Defined as 3 consecutive VL tests  $\geq 50$  copies/ml, with at least 4 weeks between the first and last test. One of these 3 tests may be a repeat of the same sample. There are a number of alternative definitions for virological rebound, each of which has advantages and limitations (28). The alternative definitions to be used in this trial will be described in the full statistical analysis plan.

- **CD4+ count change**  
Defined as change from baseline in absolute CD4+ count.
- **Health-related Quality of Life change**  
Defined as change from baseline in the mental and physical health summary scores.
- **Neurocognitive function change**  
Defined as change from baseline in the neurocognitive function summary score.
- **Cardiovascular risk change**  
Defined as change from baseline in the risk of cardiovascular disease calculated from the Framingham equation (19).
- **Health care costs**  
Defined as the total cost of health care resources utilised per patient year.

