## APPENDIX 7: DIAGNOSTIC CRITERIA FOR SERIOUS AIDS-DEFINING ILLNESS

These criteria are based on the 1993 US Centers for Disease Control and Prevention criteria for category C disease (ref MMWR 1992; 41 [No RR-17]: 1-19), but excluding oesophageal candidiasis and chronic mucocutaneous herpes simplex virus infection. Events that meet either the presumptive criteria (if available) or definitive criteria will count as endpoints in this trial.

|                                                                  | PRESUMPTIVE CRITERIA                                                                                                                                                                                                                                                                                                                   | DEFINITIVE CRITERIA                                                                                                 |
|------------------------------------------------------------------|----------------------------------------------------------------------------------------------------------------------------------------------------------------------------------------------------------------------------------------------------------------------------------------------------------------------------------------|---------------------------------------------------------------------------------------------------------------------|
| CONSTITUTIONAL DISEASE                                    |                                                                                                                                                                                                                                                                                                                                        |                                                                                                                     |

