| Other extrapulmonary toxoplasmosis              | none                                                                                                                                                                                                                                                                                                                                 | symptoms plus histology or microscopy                                                     |
| NEOPLASMS                                |                                                                                                                                                                                                                                                                                                                                      |                                                                                           |
| KS, Kaposi's sarcoma                            | Typical appearance without resolution. clinicians who have seen few cases should not make presumptive diagnoses                                                                                                                                                                                                                      | Histology                                                                                 |
| Primary cerebral lymphoma                       | Symptoms consistent with lymphoma, at least one lesion with mass effect on brain scan, no response clinically and by scan to toxoplasma treatment                                                                                                                                                                                    |                                                                                           |
| B-cell, non-Hodgkin's lymphoma                  | none                                                                                                                                                                                                                                                                                                                                 | histology                                                                                 |

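### Non-fatal Hodgkin's lymphoma and non-cerebral T-cell lymphoma fit neither the AIDS nor the non-AIDS event definition, so they drop out of the secondary serious-complication composite

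*Combined protocol and SAP*

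**What the plan says.** Section 9.2.2 makes serious drug- or disease-related complications a secondary outcome: "Defined as the first occurrence of one of the following in any individual patient". The list has three parts: all-cause death, serious AIDS-defining illness by the criteria of Appendix 7, and serious non-AIDS-defining illness by those of Appendix 8. The last item of the third part is "Non-AIDS malignancy", with no exclusion stated at that point.

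Appendix 8 adds the exclusions. Its row is labelled "Non-AIDS malignancy (excluding Kaposi's sarcoma (KS), lymphoma, invasive cervical cancer", and the criterion beside it reads "Diagnosis of cancer other than lymphoma, KS or invasive cervical cancer". Neither the label nor the criterion limits lymphoma by type.

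Appendix 7 says "Events that meet either the presumptive criteria (if available) or definitive criteria will count as endpoints in this trial". Its neoplasm rows are Kaposi's sarcoma, primary cerebral lymphoma, "B-cell, non-Hodgkin's lymphoma" and "Cervical carcinoma, invasive". The primary cerebral lymphoma row opens with "Symptoms consistent with lymphoma, at least one lesion with mass effect on brain scan" and names no cell type.

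Sections 7.3 and 16.4 have the Endpoint Review Committee check reported events against these criteria. Neither section gives it discretion to accept a diagnosis that is not listed.

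**The concern.** The two appendices should be complementary for cancer: what is excluded from one as AIDS-defining should be included in the other. For lymphoma they are not. Appendix 8 excludes the whole disease group, while Appendix 7 includes only part of it. A patient whose Hodgkin's lymphoma is diagnosed and successfully treated would have no event in this composite, whereas one with any solid tumour other than invasive cervical cancer would have one under Appendix 8.

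Two things are at stake. The first is event capture in a secondary outcome that section 9.5.2 analyses by time-to-event methods, so both missed events and late event dates matter. The second is data collection in the extension. Sections 7.1.8 and 18 restrict the clinical events gathered from the notes to AIDS events, serious non-AIDS events and deaths, and section 18 drops serious adverse event reporting. Section 1.1.5 keeps disease-related complications, but not adverse events, as an extension outcome.

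**Working it through.** No figure in the plan bears on this point, so the check is a comparison of definitions.

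**Step 1: the three Appendix 8 exclusions against Appendix 7.**

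| Excluded in Appendix 8 | Counted in Appendix 7 | Match |
|---|---|---|
| Kaposi's sarcoma | Kaposi's sarcoma | Yes |
| Invasive cervical cancer | Invasive cervical carcinoma | Yes |
| Lymphoma, any type | B-cell non-Hodgkin's; primary cerebral | Partial |

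Only the lymphoma exclusion is wider than its counterpart.

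**Step 2: each lymphoma through the composite.**

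| Diagnosis | Appendix 7 | Appendix 8 | In the composite |
|---|---|---|---|
| B-cell non-Hodgkin's | Yes | No | At diagnosis |
| Primary cerebral, any cell type | Yes, if criteria met | No | At diagnosis |
| Hodgkin's, non-fatal | No | No | Not counted |
| Non-cerebral T-cell, non-fatal | No | No | Not counted |
| Either of these two, fatal | No | No | As a death, at the date of death |

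**Step 3: is the omission deliberate?** Where the authors drop a category C condition they say so: the opening of Appendix 7 names oesophageal candidiasis and chronic mucocutaneous herpes simplex as left out. Nothing names or justifies leaving out Hodgkin's or T-cell lymphoma. Section 9.2.2 points the other way, because a lymphoma absent from Appendix 7 would ordinarily be read as a non-AIDS malignancy.

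**Step 4: could the case be recorded elsewhere?** During the main trial it would be reported as a serious or grade 3 or 4 adverse event if it met those criteria (section 11.2.1), and grade III and IV events are compared between arms (section 9.5.2). That does not place it in the composite. In the extension this route closes. If sites read the two illness categories by Appendices 7 and 8, a non-fatal case belongs to none of the clinical event categories being collected.

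**The case against.** The strongest reply is that the effect is slight. Fatal cases still count as deaths. A T-cell lymphoma in the brain can count under the primary cerebral lymphoma row, and Appendix 7 also has a row for indeterminate intracerebral lesions. A case matters only if it would have been the patient's first event. The same definition applies to both randomised arms, and the documents give no reason to expect these lymphomas to be commoner in one. During the main trial most such cases would probably surface as adverse events. All of this stands. It limits the importance of the gap but does not close it.

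A second reply is that Appendix 8 says it is based on criteria from an established trials network, so the exclusion may have been inherited for comparability. The documents cannot settle that. Even an inherited wording has to fit the Appendix 7 list it is paired with here.

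A third reply is that redefining an endpoint in an open-label trial carries its own risk, since one of the two committee clinicians may be directly involved with the trial (section 16.4). This is a fair warning. It calls for blinding the change and any re-review; it does not justify leaving the gap.

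A reader might infer that every Hodgkin's and T-cell lymphoma is lost, or that the trial's main clinical safety comparison is compromised. The first goes too far for the reasons above. The second has no basis: the documents list this composite among eight secondary outcomes and do not rank it as the main safety comparison.

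**Conclusion.** The gap is real on the plan's own wording. Non-fatal Hodgkin's lymphoma and non-cerebral T-cell lymphoma are left out of the composite, and fatal cases are dated at death instead of diagnosis. In the extension, non-fatal cases may not be captured at all.

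The size cannot be estimated from the documents. A reader might try. Section 9.3 assumes uniform recruitment over 24 months within 60 months, so mean follow-up is 60 − 24/2 = 48 months, and 560 × 4 = 2,240 patient-years before losses. At an assumed 0.2 to 1 such lymphoma per 1,000 patient-years, this gives 2,240 × 0.0002 = 0.4 to 2,240 × 0.001 = 2.2 cases over both arms. Divided by an assumed 20 to 40 composite events, the share runs from 0.45/40 = 1% to 2.24/20 = 11%. The percentages should not be relied on. The documents support neither the incidence nor the event count, and the upper end pairs the highest rate with the lowest count. Nothing is subtracted for fatal cases, earlier first events or loss to follow-up.

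That the number is probably small is a judgement, not a result. What follows is some loss of events under a definition common to both arms; bias between arms has not been shown. The primary resistance endpoint, the sample size (554, rounded up to 560) and the non-inferiority conclusion are unaffected. Severity: minor.

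**What to change.** In the malignancy row of Appendix 8, in both the label and the criterion, replace *lymphoma* with *lymphomas listed in Appendix 7 (B-cell non-Hodgkin's and primary cerebral lymphoma)*. Every other lymphoma then counts as a non-AIDS malignancy, and the two appendices are complementary for lymphoma, as they already are for Kaposi's sarcoma and cervical cancer.

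Three safeguards belong with the change:

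- Make it without knowledge of results by arm.
- Tell sites before the extension notes review, so that these diagnoses are recorded as serious non-AIDS events.
- Have any lymphoma already reported re-adjudicated by the Endpoint Review Committee from documents that do not reveal the treatment arm.

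The cost is a minor protocol amendment, with the notification or approvals that section 13 requires, a note to sites, and re-review of perhaps a few event forms.
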